### Randomization, Allocation, and Blinding

Sample determination was carried out using a cluster sampling approach. The target population was all inpatient health centers spread across 11 subdistricts in Purworejo Regency. Based on data from the Health Office, 14 inpatient health centers met the inclusion criteria. Of these, 11 (78.6%) were randomly selected, each representing 1 subdistrict. These 11 subdistricts consisting of 22 pregnant class clusters (C1-C22) were randomized into an intervention group (n=11, 50%) and a control group (n=11, 50%) using the compute-generated random allocation method. A list of cluster codes was entered, and a random sequence was used to divide the groups in order. The results of randomization determined that the first 11 clusters in the list were allocated to the intervention group (C1-C11), while the remaining 11 clusters were allocated to the control group (C12-C22). Randomization was carried out by independent researchers to ensure unbiased random allocation.

The group allocation was kept secret until the intervention group received treatment. Blinding was not possible both for the treatment provider (researcher) and for the sample because the monitoring intervention allowed for active interaction between treatment provider and sample. To ensure the accuracy and completeness of the report, this study adheres to the standards set out in CONSORT (Consolidated Standards of Reporting Trials) EHEALTH V1.6 checklist (Multimedia Appendix 1), which includes a detailed description of the digital intervention and research methodology [23]. The timeline of participant participation was developed in accordance with the SPIRIT (Standard Protocol Items: Recommendations for Interventional Trials) statement (Table 2 and Multimedia Appendix 2) [24].

**Table 2 table2:** SPIRIT^a^ checklist–recommended schedule for study participation.

Study period and activities		Enrollment time point	Allocation time point	Postallocation time points				Close-out time point
		Week 1	Week 0	Month 1	Month 2	Month 3	After month 3	
**Enrollment**								
	Informed consent	X^b^	—^c^	—	—	—	—	
	Eligibility screening	X	—	—	—	—	—	
	Random allocation (intervention vs control)	—	X	—	—	—	—	
**Interventions**								
	REST^d^ app installation and training^e^	X	—	—	—	—	—	
	REST mobile app usage by pregnant women and midwives^e^	—	—	X	X	X	X	
	Routine ANC^f^ class^g^	—	—	X	X	X	—	
**Assessments**								
	Baseline clinical measurements	—	—	X	—	—	—	
	ANC visit	—	—	X	X	X	—	
	Pregnancy complications	—	—	X	X	X	—	
	Mode of delivery	—	—	—	—	—	X	
	Birth weight	—	—	—	—	—	X	

^a^SPIRIT: Standard Protocol Items: Recommendations for Interventional Trials.

^b^Applicable.

^c^Not applicable.

^d^REST: Risk Identification, Evaluation Counseling, Systematic Monitoring, Troubleshooting.

^e^Intervention group.

^f^ANC: antenatal care.

^g^Intervention and control groups.

### Intervention

The REST mobile app provides pregnant women with real-time access to test results during pregnancy, personalized health reminders, and interactive communication with midwives, empowering them to make informed health decisions immediately. To minimize delays in reaching care, the app includes a birthing site–planning feature, helps midwives direct when urgent referrals are needed, and facilitates mobilization in the case of an emergency. To address delays in receiving adequate care in health care facilities, REST supports midwives by enabling structured antenatal monitoring and facilitating prereferral communication with referral centers, ensuring that health care facilities are better prepared to receive and manage incoming patients. The REST mobile app, designed for pregnancy monitoring from early pregnancy to delivery, has been officially copyrighted by the Ministry of Law and Human Rights of the Republic of Indonesia (ID: 000655305).

Before starting the intervention, the midwives were first given face-to-face training on the use of apps and procedures for implementing the ANC class. This joint intervention was deemed necessary to ensure consistent use of the platform during the trial. Next, training was continued for the participants of the ANC class regarding how to use and fill in the app. A handbook for using the app was also provided to all participants in the intervention group. Participants in the control group received standard ANC class services, as outlined by Indonesia’s national maternal health program. These services include providing health education, nutrition counseling, and pregnancy gymnastics activities in accordance with meeting materials in ANC classes conducted by midwives. No digital tools or mobile apps were introduced to this group. Educational materials were delivered in print format as per standard practices, and no structured training or technological support was provided. This approach ensured that any differences in outcomes observed between the control and intervention groups could be attributed to the use of the REST mobile app.

The intervention that was implemented was in the form of a Template for Intervention Description and Replication (TIDieR), as shown in Table 3 [25].

**Table 3 table3:** The TIDieR^a^ format.

Item number	Item name	Description
1	Intervention	Use of the REST^b^ mobile app
2	Reasons for the intervention	Lack of discipline for pregnant women to participate in government program activities that support pregnancy health, such as ANCc classes. The ANC class is a monitoring effort to improve the welfare of mothers and babies. Monitoring using the REST mobile app is expected to make it easier for pregnant women and midwives to monitor the health condition of mothers.
3	Action	Providing assistance to mothers during pregnancy using mobile apps. Assistance is provided to monitor the health condition of both mother and fetus. The mother takes part in a class for pregnant women and is examined (10 pregnancy examinations: height and weight, blood pressure, mid-upper arm circumference, uterine fundal height, tetanus immunization, iron supplement tablets, fetal presentation and fetal heart rate, counseling, laboratory tests, and case management).
4	Procedure	Conducting initial identification of mothers at the first meeting of the ANC class. Mothers are examined by midwives at every class meeting of pregnant women, and the results of the pregnancy examination are entered into the REST mobile app. Each mother gets a different evaluation from the midwife according to the results of the mother’s pregnancy examination. The ANC class is held 3 times, with a duration of approximately 90 minutes per meeting. In each implementation of the class for pregnant woman, the mother is given pretest and posttest questions.
5	Organizers	Principal investigator: ensures the readiness of activities and the completeness of the equipment needed during the ANC class. Midwife facilitator (trained in the use of mobile apps): carries out examinations of pregnant women, provides counseling, and documents examination results into mobile apps. Cadres (trained in the measurement of height, weight, and blood pressure): assist midwives during the implementation of classes for pregnant women. Enumerator (trained in the use of mobile apps): assists the principal investigator in monitoring the progress of ANC class activities.
6	Intervention delivery model	The provision of interventions was carried out face to face in each group of pregnant women. Pregnant women were required to attend classes 3 times and were also advised to fill in the results of examinations outside of the class activities so that the midwives could still monitor.
7	Venue and facilities	Pregnancy monitoring was carried out in the Purworejo Regency area. The infrastructure used was stationery, mobile phones (smartphones), weight scales and height-measuring instruments, tools to check hemoglobin levels, dopplers to check the fetal heart rate, mid-upper arm circumference tape, metline to measure the uterine fundal height, digital sphygmomanometers, and research questionnaires.
8	Changes or modifications during the process	The time of the class for pregnant woman was adjusted for the mothers and midwives according to an agreement. Pregnancy monitoring using the REST mobile app was adjusted to local conditions and the ownership of mobile phones by pregnant women. Furthermore, pregnancy monitoring using an app in the ANC class was carried out by midwives at the workplace or their respective practices.
9	Planning	On the REST mobile app, a reminder was created to remind midwives and mothers of the date of the ANC class. This reminder appeared in the form of a notification the day before the class for pregnant women was held.

^a^TIDieR: Template for Intervention Description and Replication.

^b^REST: Risk Identification, Evaluation Counseling, Systematic Monitoring, Troubleshooting.

^c^ANC: antenatal care.

The intervention given to the treatment group used the REST mobile app. The app was validated by 3 experts: an obstetrician and gynecologist, a health application expert, and a community midwifery expert. The app was piloted in a small group of pregnant woman communities who were not involved in the intervention study. Evaluation included the format, substance, presentation, and language. The results of the trial were measured by the distribution of simple questionnaires, interviews, and observations. After revision for refinement, the app was ready to use in research.

In a preimplementation survey involving 25 pregnant women and 10 midwives in Purworejo Regency, the REST app scored an average of 79.3 on the System Usability Scale (SUS), indicating above-average usability. Participants found the navigation intuitive, the language clear, and the visual design attractive. Of the 25 pregnant women, 23 (92%) successfully downloaded and used the REST mobile app independently within 3 days of onboarding. Midwives reported that training sessions only took an average of 60 minutes, and no major technical hurdles were encountered. In total, 30 (85.7%) pregnant women and midwives reported being very satisfied with the app and recommended it for use in pregnancy monitoring. To ensure cultural sensitivity and responsiveness to the needs of the target population, the study was developed in close collaboration with local stakeholders, including community health workers, midwives, and representatives of pregnant women in the study area. The content and language used in the REST mobile app were adapted to reflect local cultural norms, health beliefs, and communication styles, using Bahasa Indonesia and regionally appropriate terminology. Prior to implementation, the app and data collection instruments were pilot-tested with a sample of the target population to assess clarity, relevance, and acceptability.

Figures 1-3 show images of the validated and tested app [26]. The app display for midwives is different from that for participants; in the version for midwives, detailed data of pregnant women who are members of the ANC class group appear, monitored by each midwife.

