Assessment of the results of the research will begin from the implementation of the first class of pregnant women. The total number of meetings was 3. The final result (a comparison of the expected outcome) was at the time of delivery. The research was carried out after ethical approval was obtained. The research locations are in 11 subdistricts in Purworejo Regency (Central Java, Indonesia): Loano, Purwodadi, Bruno, Butuh, Purworejo, Bagelen, Kaligesing, Kemiri, Kutoarjo, Ngombol, and Pituruh. These 11 subdistricts were chosen because they have health centers with inpatient services that make it easier for pregnant women to give birth in their areas.

Each ANC class group consisted of 10 pregnant women and 1 midwife. In each of the 3 meetings, an examination based on the 10T pregnancy examination standard was conducted, which included measuring the weight and height (T1), blood pressure (T2), mid-upper arm circumference (T3), uterine fundal height (T4), tetanus immunization (T5), iron supplement tablets (T6), fetal presentation and fetal heart rate (T7), counseling (including childbirth and postpartum preparation; T8), hemoglobin levels (T9), and care as needed (T10), as per the policy of the Indonesian Ministry of Health [5]. The results of the examination at each meeting were entered into the REST (Risk Identification, Evaluation Counseling, Systematic Monitoring, Troubleshooting) mobile app, and the pregnant women could see these results. If they performed a self-examination outside the ANC class schedule, they could fill in the results of the examination according to what they knew. Midwives and pregnant women were provided with training and a guidebook module for using the app. The control group carried out the standard ANC class without the use of the app, and they were exempt from recording examination results.

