**Figure 3 figure3:**
[figure not shown]
Image of the REST mobile app's profile screen. Pregnant women (participants) can monitor their pregnancy based on the results of the examination that have been input by the facilitator midwife and can also fill in the results of the examination carried out outside the implementation of the ANC class. ANC: antenatal care; REST: Risk Identification, Evaluation Counseling, Systematic Monitoring, Troubleshooting.

The fidelity of the intervention was assessed through a variety of strategies. First, the REST mobile app included an internal analytics system that automatically recorded user activities, such as examination results filled in by midwives and the completion of scheduled tasks by pregnant women (recording data on ANC visits). Second, the research assistant conducted periodic monitoring during ANC classes using a standard checklist to observe whether midwives and pregnant women were using the app according to protocol. Third, participants filled in the part of the delivery results they reported themselves. Any deviations from their intended use were documented and analyzed. This combined method allowed us to evaluate the compliance and quality of application usage across the cluster. The REST mobile app includes a built-in troubleshooting and decision support feature designed to assist midwives in early identification and management of maternal health issues. This feature operates on a rule-based algorithm that evaluates input data, such as blood pressure and hemoglobin levels against reference thresholds established by the Indonesian Ministry of Health and WHO guidelines. If an abnormal value is entered, the app automatically flags the entry and provides a visual alert. It then offers a set of recommended clinical actions, such as counseling, closer follow-up, or referral to a higher-level facility. Midwives retain clinical autonomy in making final decisions, but the app serves as a structured guide to enhance consistency and responsiveness in care. This feature was designed to strengthen early detection and ensure standardization in ANC service delivery, particularly in remote or resource-limited settings.

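### The Intervention section says its control condition lets any difference be attributed to the app, but the two-arm design can estimate only the effect of the REST package

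*Protocol article*

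**What the plan says.** All of the following is in the Protocol article.

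- **Intervention, attribution.** After describing the control services, the section presents them as a guarantee: "any differences in outcomes observed between the control and intervention groups could be attributed to the use of the REST mobile app".
- **Intervention, training.** Before the intervention began, "the midwives were first given face-to-face training on the use of apps and procedures for implementing the ANC class". The next sentence reads: "This joint intervention was deemed necessary to ensure consistent use of the platform during the trial".
- **Intervention, control.** Control classes had no digital tools and used printed materials, and "no structured training or technological support was provided".
- **Study Design, control.** "The control group carried out the standard ANC class without the use of the app, and they were exempt from recording examination results".
- **Intervention, fidelity paragraph after Figure 3.** "the research assistant conducted periodic monitoring during ANC classes using a standard checklist", to see whether midwives and women used the app as the protocol required.
- **Strengths and Limitations.** The section lists selection bias, limited comparability of clusters, residual confounding, and performance and reporting bias from the lack of blinding. It says that a causal effect cannot be firmly established.
- **Conclusion.** The section speaks of the potential of the app and recommends taking it into national programmes.

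**The concern.** The attribution sentence claims a property of the design: that the comparison isolates the app. Yet the section that makes the claim describes the intervention as the app plus training that goes beyond the app, and describes control as having neither. The absence of training in control is offered as support for attributing differences to the app. In fact an unmatched component is what prevents that attribution.

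Training in class procedures and observation of classes could plausibly affect how examinations, counselling and follow-up are carried out, and so ANC visits and complications, two of the four primary outcomes. The documents give no evidence on the size of such an effect. What is at stake is the meaning of a positive result. A health office that adopted the app without the training and monitoring could not rely on the trial's estimate, although the Intervention section would tell it that it could.

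**Working it through.** The plan gives no figure on this point, and the sample size, outcomes and models do not depend on it. The check sets the descriptions of the two arms side by side and asks what the contrast estimates.

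**Inputs**

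| Component | Intervention arm | Control arm | Source |
|---|---|---|---|
| REST app | yes | no | Study Design; Intervention |
| App installation and training | yes | no (Table 2 footnotes this row to the intervention group) | Table 2 |
| Midwife training in class procedures | described, before the intervention | no equivalent described | Intervention |
| Checklist observation of app use in class | described | no equivalent described; with no app there is no app use to check | Intervention, fidelity paragraph |
| Classes allocated | 11 | 11 | Randomization, Allocation, and Blinding |
| Midwives per class | 1 | 1 | Study Design |

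**What the contrast estimates**

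Let *a* be the effect of the app, *t1* that of app training, *t2* that of class-procedure training and *o* that of observation. They are taken as additive only to keep the notation short. Let *s* be the outcome under standard classes.

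- Reading A, class-procedure training in the intervention arm only: difference = (*s* + *a* + *t1* + *t2* + *o*) − *s* = *a* + *t1* + *t2* + *o*.
- Reading B, class-procedure training in both arms: *t2* cancels and difference = *a* + *t1* + *o*.

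Under either reading the trial yields one estimated quantity for several unknowns. The mixed models in Data Analysis carry a fixed effect for the intervention, and its coefficient estimates the whole sum. Adjusting for maternal age, education, socioeconomic status, obstetric history or nutritional status cannot split it, because these covariates do not describe the components.

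The difference equals *a* only if the remaining terms sum to zero. Nothing in the design makes that so. Under Reading B the gap is smaller, because *t1* is onboarding that any use of the app would need, but *o* remains.

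**The two sections compared**

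The Intervention section says attribution to the app was ensured. Strengths and Limitations says causality is not firmly established and that performance bias may be present. Both cannot stand. The second does not repair the first, because it names neither the training nor the observation.

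**The case against.** The strongest reply is that this is an ordinary pragmatic comparison of an app, with the onboarding it needs, against usual care. The plan itself calls the training a joint intervention, Table 3 sets out staff and procedures, and Strengths and Limitations already withdraws a strong causal claim and mentions performance bias, the heading under which unequal attention falls. Much of this stands. A package trial is legitimate, and the design is not at fault for being one. The reply does not rescue the sentence that assigns any difference to use of the app.

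A reader might also infer more than the text supports:

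- **That only the app arm's midwives were trained to run ANC classes.** The Introduction says that ANC classes in general are facilitated by midwives or health workers with ANC training. The training sentence does not name an arm. The statement of no structured training follows a description of what control participants received, so it may refer to the women. Table 2's footnote covers app installation and training, not class procedures. Table 4 dates staff training July to October 2023, before recruitment from November 2023. If the midwives' training fell in that period, it may have preceded allocation and reached both arms.
- **That app-arm classes were supervised.** The checklist is described as a fidelity check on app use.
- **That the handbook is a further separate component.** It is a handbook for using the app, and so part of delivering it.
- **That the cadres and enumerator in Table 3 were extra staff in the app arm only.** Table 3 describes the intervention but does not say that control lacked them.

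**Conclusion.** Wrong as written. The claim that the control condition secures attribution to the app states a property that the two-arm design lacks. The trial can estimate the effect of the REST package as delivered against standard ANC classes. It cannot estimate the share due to the app alone, and the documents allow no figure for that share.

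The conclusion rests on what is described: trial-delivered midwife training and class observation appear only in the account of the intervention. It does not require that control midwives went without class-procedure training. If they received it, the extra components shrink to app onboarding and observation of app use, and the sentence is still too strong. The point limits what the trial may conclude. It does not invalidate the between-arm comparison.

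**What to change.** 1. Delete the attribution sentence in Intervention.
2. Define the tested contrast as the REST package (the app with its training, support and monitoring) versus standard ANC classes. Apply this in Intervention, in Table 3 item 1, which names only use of the app, and in Conclusion.
3. State whether control midwives received the class-procedure training and whether control classes were observed. Report both by arm. The revision should not assert that either was confined to one arm unless the trial records show it.
4. Reconcile Intervention with Strengths and Limitations, and name training and observation there as components that the trial cannot separate from the app.

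The cost is a narrower claim, about the package and not the app alone, plus a short report of training and observer visits by arm. No sample size, outcome or model changes.

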**Figure 1 figure1:**
[figure not shown]
Image of the REST mobile app's welcome screen. REST: Risk Identification, Evaluation Counseling, Systematic Monitoring, Troubleshooting.

**Figure 2 figure2:**
[figure not shown]
Image of the REST mobile app's activity screen. The midwife can fill in the data of the results of the mother's examination during the implementation of the ANC class, and the mother can see it in pregnant women's app version. ANC: antenatal care; REST: Risk Identification, Evaluation Counseling, Systematic Monitoring, Troubleshooting.

